### 3.8 Recruitment

All patients that are referred for the above-mentioned emergency or elective left sided colorectal resection in the nine contributing hospitals are screened for inclusion by the lead surgeons that receive the referrals and an additional rescreening by a dedicated study nurse on a weekly basis by on the basis of the local operation room program and admission files for left sided colorectal resections that meet or did meet (in case of emergency surgery) inclusion criteria.

## 4. Methods: Data collection, management, and analysis

### 4.1 Data collection methods

For collection of the outcomes the secuTrial®data management system is used. This is a validated und international used data base. Data are extracted from the individual subject file and for each enrolled patient a CRF is generated. CRF is kept current to reflect patient status during the course of the study. All data entered into the database must also be available in the individual subject file either as worksheets or as notes taken by either the investigator or another responsible person assigned by the investigator (source documentation).

Specific training for the use of secuTrial® is provided. Plausibility rules are established to promote data quality. Furthermore, data are reviewed and verified prior to data entry completion. Data quality also is improved by regular data monitoring and planned audits by the CTU Basel. 30 days after the operation, study patients are interviewed by study nurses. Postoperative complication rates are assessed. In case of unavailability of the patients, treating physicians of the study patients are interviewed.

### 4.2 Data management

The data are transferred in the above-mentioned password protected secuTrial® database. The participant-, hospital-, and physician-identification list is stored within a server of the CTU of the University Hospital Basel separate from the patient data with access limited to the PI and two other Co-PIs. For quality assurance the Ethics Committee or an independent trial monitor may visit the research sites at any time. All involved parties keep the patient data strictly confidential. The Sponsor-Investigator is responsible to plan and conduct data monitoring. All source data and project related files and documents are accessible to the monitor and questions are discussed during the monitoring visits.

### 4.3 Statistical methods

The primary objective of the study is to be measured by the CCI 30 days post-operative compared to the CCI under standard care as the control group. The average CCI of patients treated in participating hospitals before implementation of the CB will be compared with the average CCI after implementation.

We hypothesize that the CB will be effective in reducing CCI scores 30 days post-operation as compared to standard care.

H0: The average CCI of patients treated after implementation of the CB is the same as (or higher than) the average CCI before implementation.H1: The average CCI of patients treated after implementation of the CB is lower than the average CCI before implementation.

The analysis of the primary and secondary outcomes will be made based on a one-sided Fisher`s Exact Test with the assumption of an alpha level of p < 0.05 to be considered significant. A multivariable analysis will be performed to control for the above-mentioned confounding factors concerning the primary endpoint.

For adjusted analyses, the following potential confounding factors are accounted:

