### 3.5 Outcomes

The primary endpoint is the CCI at 30 days after the index procedure. The CCI is a continuous scale to measure surgical morbidity that has been developed on the basis of the Clavien Dindo Classification [28] for surgical complications and summarizes and weighs all postoperative complications to a scale from 0 (no complications) to 100 (death of the patient) [27]. This outcome allows to quantify the overall burden of complications and a more subtle detection of differences in the quality of care. It better reflects the patients’ perspective instead of solely summarizing the worst complication the patient did encounter during the course of his or her treatment.

– The first secondary endpoint is the rate of SSI at 30d.– The second secondary endpoint is the mortality rate at 30d.– The third secondary endpoint is the hospital length of stay.– The fourth secondary endpoint is the contribution margin measured as the difference between allocated costs and billed and paid income for a particular case.– The fifth secondary outcome is anastomotic leakage at 30d defined as any radiologically or clinically diagnosed anastomotic leakage.

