### 3.7 Sample size

The sample size calculation described below is for an observational study. Simulations were used to estimate the required sample size. Specifically, we generated 1111 synthetic datasets for a range of potential sample sizes and possible reductions in CCI score due to the modified standard. We then applied the intended analysis (a linear mixed effects model with CCI as the outcome) to each of the simulated datasets. We modelled adoption of the modified standard as a fixed effect and the surgery performance of each study centre as a random effect to account for expected variation in outcomes.

The simulations are based on the following assumptions.

The modified standard will be studied in eight middle sized centres (Clarunis Site Universitätsspital Basel, Kantonsspital Aarau, Spitalzentrum Biel, Kantonsspital Baselland, Luzerner Kantonsspital, Spital Limmattal, Kantonsspital Olten and Lindenhofspital Bern) and one large centre (Clarunis Site St. Claraspital).

We assume that each middle size centre contributes n patients to each condition under study (before and after adoption of the CB) and that Clarunis Site St. Claraspital contributes 2 × n patients to each study condition.

The average CCI score pre-modified standard is 30 with a standard deviation of 12.5 [27].

The standard deviation for surgery outcomes among the centres under study is 20 (based on mortality data from the participating study centres provided by the Swiss Federal Office of Public Health) [8].

We assess the change in CCI using a linear mixed model with CCI after 30 days as the outcome variable, CB implementation as a binary factor and study centre as a random effect. The hypotheses are tested applying a one-sided Wald test for the regression coefficient estimated for the CB factor at the 2.5% Level and a target power of 90%.

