We choose to use the CCI as the primary endpoint as it offers a modern and unique tool to measure and quantify the impact of all complications that happen to a given patient. It will best reflect their burden for patients and providers [9]. As a continuous parameter it allows to detect clinically relevant results with a lower sample size than for other purely event driven and therefore rarer endpoints such as mortality or anastomotic leakage [9]. By pooling the data from nine different institutions we are able to gain the target power within a reasonable amount of time (6 months for control and modified standard each).

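### Section 4.3 assigns a one-sided Fisher's exact test to the mean of a continuous CCI, contradicting the mixed model with a Wald test on which section 3.7 sized the trial

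*Protocol article*

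**What the plan says.** **Endpoint and hypothesis.** Section 3.5 makes the 30-day CCI the primary endpoint and describes it so: "The CCI is a continuous scale to measure surgical morbidity". Section 4.3 sets the alternative hypothesis on the mean: "H1: The average CCI of patients treated after implementation of the CB is lower than the average CCI before implementation".

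**Analysis in section 3.7.** The sample size comes from simulation: "We then applied the intended analysis (a linear mixed effects model with CCI as the outcome) to each of the simulated datasets". The section then specifies the model: "We assess the change in CCI using a linear mixed model with CCI after 30 days as the outcome variable". The bundle (CB) is a binary factor, centre is a random effect, and the CB coefficient is tested with a one-sided Wald test at 2.5% for 90% power. The section adds that the final models will include potential confounders and that secondary endpoints will be described only.

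**Analysis in section 4.3.** "The analysis of the primary and secondary outcomes will be made based on a one-sided Fisher`s Exact Test". The significance threshold set for this test is 5%. The next sentence reads: "A multivariable analysis will be performed to control for the above-mentioned confounding factors concerning the primary endpoint". Lists of patient and procedural factors follow. Study centre is in neither list.

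**Reason for choosing the CCI.** Section 7 argues: "As a continuous parameter it allows to detect clinically relevant results with a lower sample size".

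**The concern.** Fisher's exact test in its one-sided form compares two proportions in a 2x2 table. It does not test a difference in means. To apply it to the CCI, someone must choose a cut-off, and the protocol sets none for the primary endpoint. The only CCI threshold in the document, above 30, belongs to a secondary objective on risk factors (section 1.1). The same sentence of section 4.3 also covers length of stay and contribution margin, which are continuous.

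The article therefore names two primary analyses that differ in test, in handling of centre and in one-sided alpha (5% against 2.5%). In a non-randomised before-after study, this leaves the test, the level and possibly a cut-off open to choice once the data are seen. Following section 4.3 literally would also give up the continuous scale, which is the stated reason for choosing the CCI, and the centre term, on which the sizing rests.

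**Working it through.** **1. The two sections side by side**

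| Item | Section 3.7 | Section 4.3 |
|---|---|---|
| Primary test | Wald test in a linear mixed model | Fisher's exact test |
| Form of the CCI | Continuous | Must be binary; no cut-off given |
| Centre | Random effect | No term in the test; not in the confounder lists |
| One-sided alpha | 0.025 | 0.05 |
| Confounders | In the final models | Separate multivariable analysis, model not named |
| Secondary endpoints | Descriptive | Fisher's test, including two continuous endpoints |

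Nothing elsewhere in the article reconciles the columns.

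**2. The plan's own sample size.** The inputs, all from section 3.7, are: mean 30, patient SD 12.5, centre SD 20, effect 10, VIF 3.3.
- Final step: 45 × 3.3 = 148.5, so 149 per arm and 298 in total. This reproduces.
- Base: 8 × 10 + 20 = 100, not the stated 90. This is a separate slip, and the present point does not depend on it.

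**3. Power of the mixed model.** Both periods are observed in every centre, so the centre effect cancels from the comparison. SE = 12.5 × √(2/n) and power = Φ(10/SE − 1.96) at one-sided 2.5%.
- n = 50 per period: SE = 2.50, Φ(4.00 − 1.96) = 97.9%. Simulating the mixed model gave 98.1%.
- 149 per period with the VIF in full: 149/3.3 = 45.2 effective, SE = 2.63, Φ(3.80 − 1.96) = 96.7%, about 97%.

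**4. What ignoring centre does.** Total SD = √(12.5² + 20²) = √556.25 = 23.6. For 90% power at one-sided 2.5%, n per arm = 2 × (1.96 + 1.2816)² × SD²/10². This gives 33 with SD 12.5 and 117 with SD 23.6, even when means are compared.

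**5. Power of Fisher's test (illustrative).** The cut-off is my assumption. The CCI is simulated as normal with the inputs above, in nine centres, with the large one contributing double.
- Cut-off >30: the expected proportions are 50.0% before and 1 − Φ(10/23.6) = 33.6% after.
- Simulated power at about 150 per period:

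| Assumed cut-off | One-sided 2.5% | One-sided 5% |
|---|---|---|
| 20 | 82-83% | 90% |
| 30 | 81-82% | 89-90% |
| 40 | 75-76% | 84-85% |

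The level that section 4.3 attaches to Fisher's test is 5%, so the right-hand column describes the plan as written.

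**The case against.** **Adjustment is planned.** A reader might infer that section 4.3 offers only a crude comparison. It does not: the sentence after the Fisher sentence plans a multivariable analysis of the primary endpoint, and section 3.7 also promises confounders in the models. What remains is that this analysis has no named model, that centre is absent from its covariate lists, and that the significance criterion belongs to Fisher's test. The defect is which analysis is primary, not absence of adjustment.

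**A workable test exists.** A reader might infer that the trial has no confirmatory test that can be carried out. Section 3.7 gives one in full. The accurate statement is that section 4.3 contradicts it.

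**The power loss may be small.** A reader might infer that the trial is badly underpowered. The documents do not support that.
- At the 5% level of section 4.3, Fisher's test at about 150 per period and a cut-off of 30 reaches roughly the 90% target.
- At 50 per period it would have about 30% power at 2.5%, but that is the size before inflation, not the planned one.
- Without the VIF, the model's power at 149 per period is close to 100%. That treats the patients added for confounder adjustment as free power, so about 97% is the fair comparator.
- The caseloads in section 2.1 sum to 1,415 a year, about 706 per six-month period after rounding down by centre. If all were enrolled, Fisher's power at 2.5% would be above 99%; with half, about 98%.
- The normal model puts about 10% of control and 20% of bundle patients below zero, which the 0-100 scale does not allow.

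All of this stands, so the power figures are illustrations only.

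**The Fisher sentence may have been meant for binary endpoints.** That is possible, but it names the primary outcome explicitly, and the correction needed is the same.

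**Conclusion.** Section 4.3 is wrong as written. It assigns to a hypothesis about a mean a test that cannot address it without a cut-off that the protocol does not define, and it conflicts with section 3.7 on test, centre and alpha. It also conflicts with section 3.7 on whether secondary endpoints are tested or described, and it applies Fisher's test to two continuous ones. These conclusions rest on the text alone.

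The size of any power loss is uncertain. With an assumed cut-off of CCI >30, a normal CCI and about 150 per period, Fisher's test has about 81-82% power at one-sided 2.5% and 89-90% at 5%. The centre-adjusted model has about 97% at 2.5% with the VIF in full. The stronger reason to correct the text is that the primary analysis is not fixed before the data are seen.

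**What to change.** In section 4.3:
- Replace the Fisher sentence for the primary endpoint with the section 3.7 model as the single primary analysis: 30-day CCI as outcome, CB as binary factor, centre as random effect, pre-specified confounders.
- State one alpha, the one-sided 2.5% used for sizing, and report the mean difference with a 95% confidence interval, which matches that level.
- Say that the multivariable analysis is this model, or label it as supportive.
- Confine Fisher's test to crude comparison of the binary secondary endpoints (SSI, mortality, anastomotic leak).
- Report length of stay and contribution margin with methods for continuous data.
- Reconcile this with the statement in section 3.7 that secondary endpoints are described only.

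The cost is a change of wording in the protocol and, if there is one, the analysis plan. No new data, patients or design change are needed.

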**Highlights:**

**Purpose:**

**Methods:**

**Discussion:**

## 1. Introduction

Complications after colorectal surgery are encountered in up to 40% of patients with anastomotic leakage being the most feared potentially fatal outcome [1,2,3]. Multiple patient factors such as immunosuppression, malnutrition or severe comorbidities as well as surgeon`s and institutional factors such as caseload are known to influence the risk of complications [4,5,6]. While reported overall complication and leak rates showed only minor or no improvements over time, they differ dramatically between institutions, depending on patient`s and surgeon`s selection [5,7]. Surgical Site Infection (SSI) is a key indicator for postoperative complications in colorectal surgery. In North Western Switzerland reported anastomotic leak rates after colorectal resection range from 1.5 to 22% on an institutional level reflecting different case selection as well as surgical practice in the contributing institutions [8].

Recent research showed, that standardization is one possible measure to reduce complication rates in surgery. The introduction of the perioperative WHO Safer Surgery Checklist, for example has shown a reduction of overall operative mortality and morbidity in general surgery for high- and low-income countries [9,10]. While this has led to a widespread implementation of the checklist in most developed countries including Switzerland, only few attempts have been made to improve outcomes by standardizing the peri- and intraoperative process in colorectal surgery so far [11]. J.K. Lovely et al showed, that the implementation of an enhanced recovery pathway including preoperative analgesia, limited intravenous fluids and opiates, and early feeding, led to a significant reduction of hospitalization time in minimal invasive colorectal surgery [12]. One of the most far-reaching changes by standardization in colorectal surgery has been achieved by the introduction of the Enhanced Recovery After Surgery (ERAS) guidelines by the Society for colorectal surgery. This program, which consists of various measures for whose effectiveness there is good evidence, has had a lasting impact on the perioperative management of patients undergoing colorectal surgery [13].

Nevertheless, a number of other interventions have been found to be useful in the reduction of postoperative complications in colorectal surgery involving the following items:

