Assuming that the CB improves CCI scores by 10 points, 5 patients are needed for each study condition from each middle-sized study centre and 10 patients for each study condition from St. Claraspital. Thus, at least 10 patients should be recruited from each small study centre and 20 patients from St. Claraspital for a combined total sample of 90 patients. This sample size allows detection of an improvement on the CCI with 90% probability (power), assuming that the CB really does reduce the CCI by 10 points on average. As the study is not randomized, the models will include all potential confounders of the true association between the intervention and the outcomes in the final models. To accurately estimate this association the sample size needs to be increased by a variance inflation factor (VIF) that reflects the correlation between the intervention and the confounding factors [29]. As this is difficult to quantify, a conservative VIF of 3.3 was applied to the estimated sample size so that a total of 149 patients per arm and a total of 298 for the study. This target sample size can be realistically achieved within the study period based on current estimated caseloads in the contributing hospitals. This power calculation was performed by the statistical department of the Clinical Trial Unit (CTU) of the Department for Clinical Research of the University Basel and reviewed by an independent statistician. The CTU is a well-established and validated unit. The secondary endpoints as described above will be analysed using descriptive statistics.

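### Section 4.3 names one pooled, unadjusted Fisher test for every secondary endpoint: it does not fit two of them, ignores hospital for the other three, and conflicts with section 3.7

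*Protocol article*

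**What the plan says.** Section 4.3 (Statistical methods) sets the test: "The analysis of the primary and secondary outcomes will be made based on a one-sided Fisher`s Exact Test", at a 5% level. The next sentence limits adjustment to one endpoint: "A multivariable analysis will be performed to control for the above-mentioned confounding factors concerning the primary endpoint". The confounder lists that follow cover patient and procedural factors. Hospital is in neither list.

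Section 3.7 (Sample size) says two other things. On the secondary endpoints: "The secondary endpoints as described above will be analysed using descriptive statistics". On adjustment, because the study is not randomised: "the models will include all potential confounders of the true association between the intervention and the outcomes in the final models". The plural there reaches beyond the CCI. The same section puts hospital into the CCI model, with "CB implementation as a binary factor and study centre as a random effect", and gives the reason: it treats "the surgery performance of each study centre as a random effect to account for expected variation in outcomes".

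Section 3.5 (Outcomes) lists five secondary endpoints: SSI, mortality, length of stay, contribution margin and anastomotic leakage. Three are binary. Length of stay and contribution margin are quantitative, and no cut-points are given for either. The Introduction reports that "anastomotic leak rates after colorectal resection range from 1.5 to 22% on an institutional level reflecting different case selection as well as surgical practice".

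**The concern.** This point is about the secondary endpoints only.

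First, the three statements on their analysis (Fisher test, descriptive only, adjusted models) cannot all stand.

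Second, a one-sided Fisher test needs a two-by-two table. Length of stay and contribution margin do not give one as defined, so those two endpoints have no usable named test.

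Third, for SSI, mortality and leakage the named test pools nine hospitals into one table per endpoint. Each hospital is observed before and after the bundle, so the design offers a within-hospital comparison, and the pooled test does not use it. If hospitals with high event rates make up a smaller part of the bundle period, the pooled rate falls with no bundle effect, in the direction that the one-sided test looks for. If they make up a larger part, a real benefit is hidden. The mix could move through caseload, consent rates, or the exclusion of non-adherent centres that section 3.3 allows. SSI is the first secondary endpoint, and the Introduction treats it as a leading marker of complications, so a misread result would matter.

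**Working it through.** **Inputs from the article.**
- Planned size (3.7): 90 × 3.3 = 297, and 297 / 2 = 148.5, rounded up to 149 per period. This reproduces the stated figure. The centre counts behind the 90 add to 8 × 10 + 20 = 100; that is a separate matter and does not affect this point.
- Caseload (2.1): 350 + 120 + 200 + 85 + 270 + 100 + 85 + 80 + 125 = 1415 a year, about 707 in six months. All eligible patients are to be screened, so both 149 and about 700 per period are relevant.
- Hospital spread: leak rates of 1.5 to 22%. No SSI or mortality rates by hospital are given.

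**Assumptions.** Nine hospital rates are evenly spaced from 1.5 to 22%, with mean 11.75%. There is no bundle effect. The four highest-rate hospitals have their contribution cut by a fraction s in the bundle period, with the total held fixed. The test is one-sided at 5%.

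**Step 1: change in the crude rate.** The four highest rates average 18.16% and the other five 6.63%, a gap of 11.53 points. With equal-sized hospitals the four hold 4/9 = 44.4% of patients before, and 0.444(1 − s) / (1 − 0.444s) after.
- s = 0.20: share 39.0%, crude rate falls by 0.054 × 11.53 = 0.6 points
- s = 0.33: share 34.9%, falls by 0.096 × 11.53 = 1.1 points
- s = 0.50: share 28.6%, falls by 0.159 × 11.53 = 1.8 points

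Weighting by the section 2.1 caseloads, averaged over random assignment of rates to hospitals, also gives 0.6, 1.1 and 1.8 points.

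**Step 2: false-positive rate of a pooled test.** Approximately Φ(Δ/SE − 1.645), with SE = √(2p̄(1 − p̄)/n). For s = 0.50, Δ = 0.0183 and p̄ = 0.108:
- n = 149: SE = 0.0360, Δ/SE = 0.51, Φ(−1.14) = 12.8%
- n = 700: SE = 0.0166, Δ/SE = 1.10, Φ(−0.54) = 29%

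This approximates a pooled chi-square test. Fisher's test is more conservative, so its rates are somewhat lower.

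**Step 3: simulation of the named test, no bundle effect, caseload weights.**

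| Cut in the four highest-rate hospitals | Fisher, 149 per period | Fisher, 700 per period |
|---|---|---|
| 20% | 5.7% | 9% |
| 33% | 6.5% | 14% |
| 50% | 9.8% | 25% |

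A Mantel-Haenszel test stratified by hospital stays at about 5% throughout. Repeat runs agree to within about one percentage point.

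**Step 4: other shifts.** Moving ten points of share from the two highest-rate to the two lowest-rate hospitals gives Fisher 9 to 10% at 149 per period and 22 to 32% at 707, against 4.8 to 5.3% stratified. The reverse shift with a true odds ratio of 0.5, at 149 per period, leaves Fisher with 18 to 27% power against 35 to 42% for a hospital-stratified exact test.

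**Step 5: stable mix.** At 149 per arm, a pooled chi-square and the stratified Mantel-Haenszel test have the same power: 57.1% and 57.0% for a risk ratio of 0.5, and 26.3% and 27.0% for 0.7. Comparing exact tests with each other (odds ratio 0.5, 149 per period), pooled against stratified gives 37.8% against 39.4%, or 44.3% against 45.1%, depending on whether the large hospitals have low or high rates.

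**The case against.** The other side has real arguments.

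- **Fisher is not the settled analysis.** Section 3.7 calls the secondary endpoints descriptive. On that reading there is no test and no false-positive rate. This stands, and it is why the contradiction is part of the point. A descriptive crude difference would still carry the 0.6 to 1.8 point shift of step 1.
- **The plan expects a balanced mix.** The sample-size section assumes that each hospital contributes the same number to both periods. Enrolment takes all eligible patients at the same nine hospitals, with weekly rescreening. Section 3.3 pairs centre exclusion with extended data collection, which tends to restore a centre's share. This stands as a reason to think that large shifts are not the expected case. These are planning assumptions, though, and the analysis does not enforce them.
- **The scenarios are chosen.** Nothing in the article supports four high-rate hospitals shrinking together by 20 to 50%, and the leak range is borrowed for SSI and mortality. At the planned 149 per period the inflation is modest; the larger figures need about 700. All of this stands.
- **Model details belong in the SAP.** This is true of the exact model. But 4.3 does not leave the choice open: it names a test and limits adjustment.

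A reader might also infer that ignoring hospital costs power when the mix is stable, since Fisher's test has lower power than Mantel-Haenszel. Step 5 does not support that. The gap comes from an exact test being set against an asymptotic one, not from the missing hospital term.

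**Conclusion.** The point holds for what section 4.3 fixes. It names one pooled test for all secondary outcomes and confines adjustment to the primary endpoint, against section 3.7. The test is unusable for length of stay and contribution margin as defined. For SSI, mortality and leakage it leaves a non-randomised comparison across unequal hospitals open to any change in mix, in either direction.

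The size is illustrative: a one-sided false-positive rate of about 6 to 10% at 149 per period and 9 to 25% at about 700, against about 5% when stratified. It rests on the leak range as a stand-in and on assumed shifts of 20 to 50%. A reader might take these as the error rates to expect in this trial. The documents do not support that, because they neither show nor predict a shift of that size. No material power loss is claimed for binary endpoints under a stable mix. Because secondary endpoints are affected and the correction is cheap, this should be fixed, but it does not threaten the CCI result.

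**What to change.** In section 4.3, replace the pooled Fisher test for the secondary endpoints with analyses that condition on hospital and, where event numbers allow, on the pre-intervention confounders already collected:

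- SSI and anastomotic leakage: logistic regression with hospital effects.
- Mortality, where events will be sparse: a hospital-stratified analysis (Mantel-Haenszel or exact) or a penalised model.
- Length of stay and contribution margin: a regression suited to the quantitative scale, with hospital effects.

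Report each as an adjusted before-after effect with a confidence interval, and keep crude rates as description. Reconcile the two statements in section 3.7 with section 4.3, so that the article says once whether the secondary endpoints are tested, modelled or only described.

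The cost is wording and a little more analysis. No new data are needed, since hospital identity and the confounders are already recorded. One small downside is that the mortality model can carry few covariates. Conditioning on hospital removes the effect of hospital mix only; it does not remove a time trend within hospitals.
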